### Collection of biological specimens

An overview of the collection of biological specimens for the ALL and brain tumor cohorts is provided in Tables 2 and 3. For children with ALL, blood and stool will be collected at five timepoints (at diagnosis, at the end of induction, at the beginning of maintenance, at the end of treatment and 1 year after the end of therapy) representing times in which fluctuations in nutritional status have been reported. For the brain tumor cohort, the initial collection is after surgery, with further collections at 3-month intervals until one year after the end of treatment. Blood samples are obtained during a routine blood draw in serum separator tubes, centrifuged, and stored at −80°C until shipped for long-term storage at IARC. Stool samples are collected in the hospital or the home setting using a specified protocol. The collected stool is stored on fecal occult blood test cards and cryovials until shipped for long-term storage at IARC.

**Table 2 pone.0319110.t002:** Summary of data collection: acute lymphoblastic leukemia cohort.

	Timepoint 1	Timepoint 2	Timepoint 3	Timepoint 4	Timepoint 5
	Diagnosis	End of induction	Beginning of Maintenance	End of Treatment	1 Year Post-End of Treatment
Timepoint window	Collect ± three working days	Collect ± three working days	Collect ± one month	Collect ± one month	Collect ± one month
STUDY INSTRUMENTS					
Demographics survey: WHO World Health Survey	x		x	x	
Food security survey: FIES	x				
Quality of life survey: PedsQL	x	x	x	x	x
Physical activity survey: PROMIS	x	x	x	x	x
Dietary data: Food Frequency Questionnaire and Nutrition support form	x	x	x	x	x
MEDICAL DATA					
Clinical data and disease characteristics	x	x	x	x	x
Anthropometrics: height, weight, MUAC	x	x	x	x	x
BIOLOGICAL SAMPLES					
Blood collection	x	x	x	x	x
Stool collection	x	x	x	x	x

*Abbreviations*: WHO, World Health Organization; FIES, Food Insecurity Experience Scale; PedsQL, Pediatric Quality of Life; PROMIS, Patient Reported Outcome Measurement Information System; MUAC, mid-upper arm circumference

**Table 3 pone.0319110.t003:** Summary of data collection: brain tumor cohort.

	Timepoint 1	Timepoints 2–8	Timepoint EOT	Timepoint EOS
	Diagnosis or Post-surgery	Repeat every 3 months from timepoint 1 until the end of treatment	End of treatment	End of Study, 1 Year Post-End of Treatment
Timepoint window	Collect after surgery/biopsy but prior to initiation of chemotherapy or radiation	Collect ± 14 days	Collect ± 14 days	Collect ± 1 month
STUDY INSTRUMENTS				
Demographics survey: WHO World Health Survey	x		x	x
Food security survey: FIES	x			
Quality of life survey: PedsQL	x	x	x	x
Physical activity survey: PROMIS	x	x	x	x
Dietary data: Food Frequency Questionnaire and Nutrition support form	x	x	x	x
MEDICAL DATA				
Clinical data and disease characteristics	x	x	x	x
Anthropometrics: height, weight, MUAC	x	x	x	x
BIOLOGICAL SAMPLES				
Blood collection	x	x	x	x
Stool collection	x	x	x	x

*Abbreviations*: EOT, end of treatment; EOS, end of study; WHO, World Health Organization; FIES, Food Insecurity Experience Scale; PedsQL, Pediatric Quality of Life; PROMIS, Patient Reported Outcome Measurement Information System; MUAC, mid-upper arm circumference

Participating institutions will batch ship blood and stool specimens yearly, sending only those from participants who have completed the study to IARC for biobanking. Prior to shipping, packaging will be inspected for contamination and humidity cards will be replaced along with dessicant packs, if indicated by the indicator located on the humidity cards. Specimens will be shipped on dry ice using an overnight courier that can properly handle biological specimens and has an established collaboration with IARC.

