Children with brain tumors face similar challenges related to nutrition, although much less data is available. Undernutrition has been observed in 31% of children with medulloblastoma and other aggressive tumors at diagnosis [16], and it has been reported that up to 94% of children with medulloblastoma and 39% of children with other central nervous system tumors develop undernutrition during treatment. [17] Further, approximately 40% of children with brain tumors experience swallowing difficulties [18,19], which contribute to decreased oral intake and further decline in nutritional status. At the same time, the development of overweight/obesity is commonly observed in children and adolescents with hypothalamic damage due to radiation therapy, surgery, or by the tumor itself [20], resulting in endocrinopathies such as diabetes insipidus and central precocious puberty. [21] In one of the few reported European cohorts of survivors of a childhood brain tumor, a higher prevalence of overweight/obesity was observed as compared to the general population (29% compared to 13%, respectively) [21] as well as a greater percent of fat mass compared to non-cancer controls (mean difference 4.1%, 95% confidence interval 2.0–6.1). [22]

More recently, it has been reported that the duration of “aberrant nutritional status” (the time at which children are in an ‘at-risk’ nutrition state during treatment) appears to be more consistently associated with poor clinical outcomes. [5,23] However, the mechanisms by which nutrition impacts these outcomes are largely unknown. [24] Genetic predisposition [25,26], microbial environment [6] or parental feeding behaviors [27] may be responsible for excess weight gain. In children with ALL, remission induction therapy significantly reduces bacterial diversity in the gut and may contribute to the development of obesogenic microbial profiles. [28] The frequent use of antibiotic therapy during the induction phase of therapy causes additional insult to the intestinal microbiota, further augmenting this phenotype. [29] Unfortunately, much of the existing data are in children with ALL, with little information on the underlying mechanisms in children with brain tumors. Moreover, most findings are limited to children residing in North America.

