## Materials and methods

### Study design

The EPIC*kids* study (clinicaltrials.gov NCT05375617) is a prospective, observational, multinational cohort study recruiting children and adolescents with newly diagnosed ALL or favorable biology brain tumors and following participants from diagnosis until 1-year after the end of treatment (EOT). Recruitment began in June of 2023 and will continue through December 2028. Completion of the study is expected in January 2031, with analysis anticipated to be performed upon study completion. EPIC*kids* is being co-led by the International Initiative for Pediatrics and Nutrition (IIPAN), Columbia University Irving Medical Center (CUIMC) and the International Agency for Research on Cancer/World Health Organization (IARC/WHO).

Eligible participants are children and adolescents diagnosed with ALL meeting the following criteria: (1) aged between 3 and 21 years old at diagnosis with B-cell ALL, T-cell ALL, or mixed phenotype acute leukemia confirmed on immunophenotyping by flow cytometry and receiving standard leukemia treatment at one of the participating centers or may be children on a clinical trial or “as per” a clinical trial. For the brain tumor cohort, eligible children are: (1) aged between 3 years and 21 years old at the time of diagnosis with a favorable biology brain tumor (tumors with expected 5-year survival > 70%) confirmed by either pathology report, imaging and/or biochemical studies including low-grade gliomas, some medulloblastomas, ependymomas, pituitary tumors, germ cell tumors, and (2) receiving standard treatment at one of the participating centers with surgery, chemotherapy, radiation therapy or may be children on a clinical trial or “as per*”* a clinical trial. Children receiving autologous stem cell transplantation as part of their regimen may be included. Participating centers enrolling children and adolescents are listed in Table 1.

**Table 1 pone.0319110.t001:** Participating centers in EPIC*kids* cohort.

Institution Name	Location
Aghia Sofia Children’s Hospital	Athens, Greece
Fondazione IRCCS San Gerardo dei Tintori	Monza, Italy
Fondazione IRCCS Istituto Nazionale dei Tumori	Milan, Italy
Hospital Vall D’Hebrón	Barcelona, Spain
Pediatric Cancer Center Barcelona, Hospital Sant Joan de Déu	Barcelona, Spain
Hospital Infantil Universitario Niño Jesús	Madrid, Spain
Hospital Universitario La Paz	Madrid, Spain
Hospital Universitario Virgen del Rocío	Seville, Spain

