We anticipate utilizing these data to estimate the power and sample size needed for future intervention studies, as well as answer some basic research questions such as: 1) How does dietary intake fluctuate during and after treatment for ALL or a brain tumor?; 2) What is the effect of treatment on nutritional status, defined by anthropometric measures (severely underweight, underweight, healthy weight, overweight, or obese) at baseline and at follow-up assessments? 3) What is the association between poor quality of life and nutritional status over the course of treatment? 4) What are the associations between food security, nutritional status (anthropometric), dietary intake, and treatment-related toxicities? 5) What are the overall trends of the aforementioned nutritional indicators and determinants (dietary intake, nutritional status, HRQOL, socioeconomic status) during the course of therapy? and 6) How are these nutritional indicators associated with survival in children with cancer? These analyses will allow the researchers and staff members to develop lifestyle interventions that may be tested through controlled, randomized trials to further improve outcomes among children with cancer.

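### The ALL baseline window is set around diagnosis, not before the first dose, so untreated and on-treatment blood, stool and anthropometric baselines can be mixed

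*Protocol article*

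**What the plan says.** **ALL cohort.** The section on collection of biological specimens states that "blood and stool will be collected at five timepoints (at diagnosis, at the end of induction" and at three later points. Table 2 labels Timepoint 1 as diagnosis and gives its window as "Collect ± three working days". Blood, stool, height, weight and mid-upper arm circumference are all due then. Neither the table nor the text mentions the first dose of any treatment.

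**Brain tumour cohort.** The same section says "For the brain tumor cohort, the initial collection is after surgery". Table 3 labels the timepoint "Diagnosis or Post-surgery" and sets the window as "Collect after surgery/biopsy but prior to initiation of chemotherapy or radiation". The eligibility text under Study design counts surgery as treatment: children are "receiving standard treatment at one of the participating centers with surgery, chemotherapy, radiation therapy".

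**Why timing matters, in the article's own terms.** The Introduction says that in ALL "remission induction therapy significantly reduces bacterial diversity in the gut", and that antibiotics during induction disturb the intestinal microbiota further. The Statistical analysis section plans to relate microbiome composition and diversity to nutritional outcomes, toxicities and survival. Its second research question is "What is the effect of treatment on nutritional status, defined by anthropometric measures", assessed at baseline and at follow-up.

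**Relevant safeguards.** Clinical data collection includes prospective recording of selected medications, with steroids and antimicrobials as examples. The food frequency questionnaire at baseline covers diet before diagnosis.

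**The concern.** Timepoint 1 is the reference for change over treatment and the source of baseline exposures. If some ALL children are sampled before induction and others after it has begun, the variable called baseline measures two different things. For a microbiome endpoint, part of the treatment effect may already be in the reference value, so the change to end of induction is measured from the wrong starting point. An association between baseline microbiome and later toxicity could likewise partly reflect early treatment or antibiotics instead of the child's state at diagnosis.

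The window is a rule the article states, not a detail it leaves out, and the pre-treatment condition appears for one cohort but not the other. A missed pre-treatment specimen cannot be collected later.

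A narrower issue arises for brain tumours. Where surgery is performed, Timepoint 1 follows it, so a treatment effect measured from that point leaves out any effect of the operation.

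**Working it through.** The article gives no sample-size or power figure on this point to reproduce. The check compares the timing rules, with a small amount of arithmetic.

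**1. The two Timepoint 1 rules side by side**

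| | ALL (Table 2) | Brain tumour (Table 3) |
|---|---|---|
| Anchor | Diagnosis | Diagnosis or after surgery |
| Window | ± three working days | After surgery or biopsy |
| Must precede chemotherapy or radiation? | Not stated | Yes |
| Must precede surgery? | Not applicable | No |

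**2. Working days converted to calendar days** (assumes a Monday-to-Friday week and no public holidays)

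| Day of diagnosis | Third working day after | Calendar days |
|---|---|---|
| Monday | Thursday | 3 |
| Tuesday | Friday | 3 |
| Wednesday | Monday | 5 |
| Thursday | Tuesday | 5 |
| Friday | Wednesday | 5 |
| Saturday | Wednesday | 4 |
| Sunday | Wednesday | 3 |

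The latest in-window ALL specimen is therefore 3 to 5 calendar days after diagnosis, and more with holidays.

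**3. Possible treatment exposure before an in-window specimen.** The article does not give the interval from diagnosis to first induction dose. Assume it lies between 0 and 5 days. For a specimen on day 5, exposure is 5 − 0 = 5 days at one extreme and 5 − 5 = 0 days at the other. The window permits on-treatment collection; it does not show how often that happens.

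**4. What mixing does to a change from baseline.** Let Δ be the true shift from untreated baseline to end of induction, p the share of baselines taken on treatment, and f the average fraction of Δ already completed when those were taken. If p is unrelated to the child's untreated value:

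- mean recorded baseline = untreated mean + p × f × Δ
- expected recorded change = Δ × (1 − p × f)

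The proportion of the shift that is lost is p × f. The article supplies neither p nor f. Purely as an illustration, with p = 0.40:

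- f = 0.25 gives 0.40 × 0.25 = 10% lost
- f = 1.00 gives 0.40 × 1.00 = 40% lost

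The number of children affected is 900 × p, which may be anything from 0 to 900.

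**5. Which baseline measures are exposed.** For ALL: blood, stool and anthropometrics. The dietary baseline is not, because it asks about the period before diagnosis. For brain tumours, Timepoint 1 precedes chemotherapy and radiation, and only surgery can come before it.

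**The case against.** Several defences have weight.

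- **Medication records.** Steroids and antimicrobials are recorded prospectively, and the Statistical analysis section says confounding will be handled with directed acyclic graphs. This may let analysts identify and adjust for on-treatment specimens. It stands as partial mitigation, but it does not restore an untreated specimen, and no rule says how such specimens are to be classified.
- **A condensed article.** Date and time fields belong in the case report form, and their absence from an article is no defect. That is accepted. The point rests on the window that the article does state.
- **Limited stakes.** The study builds a resource, hypothesis-driven projects are to be planned separately, and no confirmatory change-from-baseline estimand is fixed. This lowers the stakes. It also means many later projects will share the same baseline.
- **A post-surgical brain tumour baseline is openly stated.** Where diagnosis rests on pathology, eligibility is confirmed only once tissue is available. This stands, so for that cohort a clear statement of scope is enough.

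A reader might also infer stronger claims that the document does not support:

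- **That neither cohort's baseline is tied to treatment.** Table 3 ties the brain tumour baseline to before chemotherapy and radiation.
- **That all 1,400 brain tumour children lack a pre-operative measurement.** Table 3 allows for biopsy, and Study design allows confirmation by imaging or biochemistry, so some children may have had no resection. The most that can be said is that the schedule does not require a pre-operative value.
- **That sicker children are treated sooner and sampled later, giving differential bias.** This is plausible, but nothing in the article supports it.

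**Conclusion.** The point holds for ALL biospecimens and anthropometrics at Timepoint 1. A specimen taken up to 5 calendar days after diagnosis, with induction or antibiotics already under way, complies with the stated window. By the article's own account, those treatments alter the gut microbiome.

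The size cannot be fixed from the document. The affected share of the 900 planned ALL children is not given, nor is the time from diagnosis to first dose. The lost proportion of a treatment shift is p × f, and the 10% to 40% shown above depends wholly on assumed values. A share such as 30% to 60% on treatment (270 to 540 children) would be a guess. The direction is also uncertain outside microbial diversity: an early or transient change in weight could move the result either way.

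For brain tumours the valid remainder is narrow: where surgery is done, baseline follows a component that the article lists as treatment, so the effect measured from it excludes surgery.

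**What to change.** **ALL, Table 2.** State that Timepoint 1 blood, stool and anthropometrics are to be collected before the first induction dose where possible, without changing when treatment starts. Keep specimens obtained later within the existing window, but flag them as on-treatment. Base the flag on the date and time of the specimen and of the first steroid, chemotherapy and antimicrobial dose. Stratify by the flag, or exclude flagged specimens, in a sensitivity analysis of any result that uses baseline.

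**Brain tumour cohort.** Either abstract pre-operative height and weight from the chart where available, or state that treatment-effect questions refer to the period after surgery.

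**Cost.** A change to the window wording, a few date-time fields, and some chart abstraction. Fewer ALL specimens will count as untreated baseline, by an amount that is unknown in advance and may not be small. None need be discarded. The change is worth making early: the article reports 72 children recruited against a target of 900 + 1,400 = 2,300, or 72 / 2,300 = 3.1%, and forms are locked once verified.

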### Survey instruments

This study has five standardized surveys (Tables 2 and 3), either available in the native language of the country (English, Spanish, Italian, and Greek) or following appropriate forward/back translation and pilot tested among patients. *For surveys not available in the native language of the participating site, forward and back translations were performed by individuals fluent in English and the local language (Spanish, Italian, or Greek). Discrepancies between versions were confirmed by an individual not involved in the translation of the survey and who was bilingual in English and the local language. Surveys were then pilot-tested for comprehension in patients visiting the oncology in- or out-patient setting.* The surveys are administered to the parent/participant by the local research personnel in their primary language. Questionnaire responses will be entered directly into the REDCap system and stored for analysis. [32,33] The REDCap database was selected as the electronic Case Report Form (CRF) platform because it is user-friendly, generates real-time reports, and data can easily be extracted for further analysis. Additionally, the REDCap mobile app’s utility [34] allows flexibility in administering the surveys to participants. A summary of the instruments is provided below.

#### Health-related quality of life.

Health-related Quality of Life (HRQOL) is defined as the extent to which an individual’s usual or expected physical, emotional, and social well-being is affected by a medical condition or its treatment. The Pediatric Quality of Life (PedsQL) Generic Core Scales have been validated in pediatric oncology populations [35] and consist of 23 items, with a parent proxy report for ages 2–4 years, 5–7 years, 8–12 years, and 13–18 years and child self-report for ages 5–7 years, 8–12 years, and 13–21 years, yielding scores within the domains of Physical, Emotional, Social, and School Functioning. [36] The PedsQL survey responses are reverse-scored and transferred to a 0–100 scale. To reverse the score, the 0–4 responses will scale to 0–100: 0 = 100, 1 = 75, 2 = 50, 3 = 25, and 4 = 0. The scores are then averaged to a final scale score, computed as the sum of the items divided by the number of items answered, with higher scale scores indicating better HRQOL.

#### Food Insecurity Experience Scale (FIES).

The FIES [37] is a metric of the severity of food insecurity at the household or individual level and relies on direct yes/no responses to eight brief questions regarding access to adequate food. It is a statistical measurement scale similar to other widely accepted statistical scales designed to measure unobservable traits such as aptitude/ intelligence, personality, and a broad range of social, psychological, and health-related conditions. The order in which the eight FIES questions are asked follows the standard order survey module, in which questions refer to conditions that move roughly from less severe to more severe food insecurity. The FIES survey module is available in 200 languages, including those at all of the participating sites. The FIES survey module can be applied using different reference periods (30 days or 12 months). When the FIES is being applied to identify risk factors and consequences of food insecurity rather than for population monitoring, a 30‐day reference period is recommended.

#### Physical activity.

The Patient Reported Outcome Measurement Information System (PROMIS) Pediatric Physical Activity survey is a validated, eight-item survey developed at the United States National Institutes of Health. [38,39] The survey assesses a child’s performance of activities that require physical actions which reflect the level of bodily movement, ranging from simple static behaviors with minimal muscle activity to more complex activities that require dynamic or sustained muscle activity and greater body movement. Physical activity behaviors are performed across non-hierarchical contexts related to the purpose (e.g., self-care, sports, school, recreation), physical environment (e.g., school, home, community), and social situations (e.g., alone, family, peers). Participants ≥8 years old will complete the self-report survey, and the parent will complete the parent-proxy survey. For participants ≤7 years old, parents will complete the parent-proxy survey on behalf of their child.

#### Demographics survey.

Demographic data will be obtained utilizing an adapted version of the WHO’s World Health Survey (2002) emphasizing parental employment and education. [40]

#### Food Frequency Questionnaire (FFQ).

The detailed quantitative FFQ developed for this EPIC*kids* cohort study is based upon FFQs used in previous cohort studies investigating detailed dietary habits. [41] In addition to information regarding the frequency of consumption and the portion size usually consumed, this FFQ also includes extra specifications about the type of food usually consumed (e.g., fat or sugar content, cooking method, etc.). [41] The experience gained from the EPICSoft/GloboDiet methodology [42] implemented in many countries across the world was crucial to building the food lists and providing data and pictures (visual aids) used for estimating portion sizes.

The tool consists of approximately 100 food categories (e.g., root vegetables, poultry, cakes), grouped into 18 food groups (e.g., cereals, non-alcoholic beverages). This FFQ survey was standardized for all countries. The local, country-specific FFQs were generated by tailoring the FFQ to the local contexts and study population (e.g., including country-specific food lists). The FFQ is accompanied by a food image book featuring validated GloboDiet photos for foods and household measures (e.g., different sizes of a common glass) to aid participants in reporting actual intakes. The purpose of the FFQ is to obtain frequency and portion size information about food and beverage consumption over a designated period (previous month). EPIC*Kids* participants will be queried about their intake over the preceding month at each timepoint, with the baseline dietary intake assessment investigating the patients’ diet before diagnosis. To calculate the usual daily intake of foods, the frequency of consumption (in times per day) will be multiplied by the selected habitual portion size. Additional information regarding cooking method, source, fat/sugar content, etc., will be used to facilitate the matching with foods included in food composition tables to allow the computation of nutrient intakes. A relative validation of this FFQ is ongoing in a pilot sample where 3-day consecutive food diaries are being collected from the same participants in addition to the FFQs. In addition, this Food Frequency Questionnaire (FFQ) will be further validated through comparison with concentration biomarkers (nutritional biomarkers in serum) using the blood samples collected from the cohort participants.

